#### Incidence of hyperplastic polyps.

The incidence of hyperplastic polyps will be examined through endoscopy and biopsy. Once the development of a hyperplastic polyp is identified, the investigators will have to report its occurrence by recording this information on the eCRF without delay.

### Sample size calculation

On the basis of previous studies, we assumed that the 10-year incidence of adenoma and adenocarcinoma in the control group is approximately 10% [5,19]. The incidence of adenoma and adenocarcinoma will decrease by 50% after *H. pylori* eradication. According to this assumption, if the primary endpoint is exponentially distributed in both groups, the expected hazard ratio (HR) for the treatment group is 0.49. One interim analysis will be planned using the O’Brien-Fleming spending function at 50% of the total primary endpoint events. A total of 66 primary endpoint events will yield approximately 80% power to detect a HR of 0.49 with an overall type I error of 0.05 (two sided). Considering a 10% dropout rate, 984 randomized patients will be enrolled. The sample size will be calculated using PASS 15 software (NCSS, LLC, Kaysville, Utah, USA).

### Interim analysis

One interim efficacy analysis will be planned for the primary endpoint by using the O’Brien-Fleming spending function at 50% of the total primary endpoint events. The primary endpoint will be tested at a two-sided nominal type I error of 0.003. The final efficacy analysis will be performed after approximately 66 primary endpoint events are observed. The primary endpoint will be tested at a two-sided nominal type I error of 0.049. The alpha spending for interim and final analyses based on the planned number of primary endpoint events is summarised in Table 1. The actual alpha spending will be based on the actual number of primary endpoint events included in the analyses and determined by the O’Brien-Fleming spending function at the time of interim and final analyses.

**Table 1 pone.0320903.t001:** Alpha spending in group sequential design using the O’Brien Fleming spending function for the primary endpoint.

First Interim Efficacy Analysis		Final Efficacy Analysis	
# Events needed	2-sided Nominal Alpha	# Events needed	2-sided Nominal Alpha
33	0.003	66	0.049

### Data management and monitoring

Data will be collected using a web-based eCRF developed by Procuratio®. The eCRFs will be completed at study enrollment and during follow-up outpatient visits. This system will anonymise and secure all data. Authorized staff members will enter the data into the electronic database, ensuring it is accurate and complete. This trial will be monitored by an independent data and safety monitoring board (DSMB) organized by independent experts, including a biostatistician.

### Safety monitoring

Adverse events (AEs) and serious adverse events (SAEs) will be documented from the moment the patient signs the informed consent form until the follow-up period ends. The investigator must notify the Ethics Committee and/or the Regulatory Authority of any AEs or SAEs, as per local regulations.

### Statistical analysis

#### General considerations.

The full details of the statistical analyses will be described in the Statistical Analysis Plan (SAP), which will be finalised prior to code breaking. Analyses will be performed using SAS software (SAS Institute, Inc., Cary, North Carolina, USA); The version used will be specified in the SAP. Categorical data will be summarised by the number and percentage of subjects in each category. Continuous variables will be summarised by descriptive statistics, including the number of observations, mean, standard deviation, median, minimum, and maximum.

We will use the Kaplan-Meier method to calculate the cumulative incidence of adenoma, adenocarcinoma, and hyperplastic polyps, as well as overall survival. These will be compared between the two treatment groups using the log-rank test. The HRs, with 95% CIs, will be estimated using a Cox proportional hazards model. The improvement rate of precancerous lesion and the eradication rate of HP will be compared between treatment groups using the Chi-square test or Fisher’s exact test.

Unless otherwise stated, all efficacy analyses (except for the primary endpoint) will be conducted with a two-sided test at a significance level of α = 0.05.

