**Methods:**

After curative gastrectomy, patients with HP infection and pathologically proven stage 1 tumors will be enrolled and randomly assigned to eradication (n = 492) and placebo (n = 492) groups. Patients in the eradication arm will be given the eradication regimen, which will comprise 40 mg of esomeprazole, 1 g of amoxicillin, and 500 mg of clarithromycin twice a day for 14 days. The primary endpoint is the development of gastric neoplasms, including adenoma or adenocarcinoma. The secondary endpoints are the 10-year overall survival, improvement rates of gastric glandular atrophy and/or intestinal metaplasia, and incidence of new-onset hyperplastic polyps among the groups.

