In contrast to the widely studied remarkable reduction in the incidence of gastric neoplasms after endoscopic resection but preserving entire stomach, the effect of HPE on the condition of the remaining stomach after distal or subtotal gastrectomy has been rarely investigated [7–9]. Theoretically, after surgery, the acidic condition within the stomach is inevitably changed because of alkaline reflux from small intestine, markedly reduced parietal cell volume, and denervation of vagus nerve. Based on these postoperative changes, some recent studies reported even spontaneous remission of HP in the remained stomach [10–14]. On the contrary, a previous study showed the potential role of eradication therapy after distal gastrectomy, which can improve precancerous lesions, such as glandular atrophy or intestinal metaplasia, in the remnant stomach [7]. Another study reported that the HPE rate of patients who underwent subtotal gastrectomy is similar to that of patients who did not undergo surgery, and the atrophy and intestinal metaplasia scores were significantly lower in the successful eradication group than in the other group [9]. On the basis of these findings, both studies recommended HPE after subtotal gastrectomy. In addition, a large retrospective study demonstrated remarkable prognostic benefits, namely, overall and gastric cancer-specific survival, in patients who received HPE therapy compared with those who did not have the same treatment [8]. However, studies have yet to elucidate whether HPE can effectively and directly prevent the occurrence of remnant stomach neoplasms after curative gastrectomy to provide high-level evidence. Consequently, in the patient group who receive surgery, the necessity of HPE was not proven and included in the current treatment guideline. To fill this gap, we aim to determine whether HPE can reduce the development of gastric neoplasms occurring in the remnant stomach after curative gastrectomy through a double-blinded, randomized controlled trial (RCT).

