### Objectives

Primary objective. This study aims to evaluate the effect of HPE on the occurrence of gastric neoplasms, including adenoma or adenocarcinoma, in the remnant stomach of patients who undergo curative gastrectomy for gastric cancer. The follow-up period for assessing these outcomes will be 10 years.Secondary objectives. This study aims to examine the following: 1) 10-year overall survival, 2) improvement rates of gastric glandular atrophy and/or intestinal metaplasia, and 3) incidence of new-onset hyperplastic polyps among the groups.

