### Secondary endpoints

#### Overall survival.

All deaths of the enrolled patients during the trial will be reported to evaluate overall survival.

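### Kaplan-Meier is fixed as the estimator of 10-year cumulative incidence for endpoints that exclude death, so absolute incidences and their difference will be modestly overstated (minor)

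*Protocol article*

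**What the plan says.** The General considerations part of the Statistical analysis section names the estimator: "We will use the Kaplan-Meier method to calculate the cumulative incidence of adenoma, adenocarcinoma, and hyperplastic polyps". The same sentence applies it to overall survival. The arm comparison follows: "These will be compared between the two treatment groups using the log-rank test", and "The HRs, with 95% CIs, will be estimated using a Cox proportional hazards model".

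The endpoint is defined without death. The abstract says: "The primary endpoint is the development of gastric neoplasms, including adenoma or adenocarcinoma". The Outcome measurements section defines both the neoplasm endpoint and the hyperplastic polyp endpoint by endoscopy and pathology only. Deaths are collected for a separate purpose: "All deaths of the enrolled patients during the trial will be reported to evaluate overall survival". The horizon is set under Objectives: "The follow-up period for assessing these outcomes will be 10 years".

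The article does not mention competing risks or say how event-free deaths enter the neoplasm and polyp analyses. It does defer detail: "The full details of the statistical analyses will be described in the Statistical Analysis Plan (SAP".

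**The concern.** Kaplan-Meier has no place for a patient who can no longer have the event. When it is applied to an endpoint that excludes death, the standard handling is to censor at death. The estimator then treats the dead patient as still able to develop a remnant neoplasm later, at the same rate as the survivors. The result is a risk under the hypothetical removal of death, not the cumulative incidence that the article says it will calculate. It is never lower than the actual incidence and is higher whenever patients die event-free.

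That can happen here. Entry is allowed up to age 70 and follow-up lasts 10 years. The Discussion says that remnant tumours take at least about 7 years to appear, so many competing deaths could come before the main period of risk. The Introduction also cites a retrospective study reporting "remarkable prognostic benefits, namely, overall and gastric cancer-specific survival, in patients who received HPE therapy", so mortality might differ between arms.

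At stake are the absolute figures. The sample size section frames the target as a 10-year incidence that is halved, and the Conclusions expect the results to shape management. Readers will take 10-year risks and their difference from these curves.

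**Working it through.** **Inputs from the protocol article.** Control 10-year incidence 10%, halved by eradication to 5%; hazard ratio 0.49; 66 events; about 80% power; two-sided alpha 0.05 (all from Sample size calculation); 10 years of follow-up (Objectives).

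**Assumed input.** 10-year mortality is not given. I use a range of 5% to 20%.

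**Step 1. Reproduce the plan's own figures.** With exponential times, HR = ln(0.95)/ln(0.90) = 0.487, which rounds to the stated 0.49. Freedman's formula at 0.487 gives 66 events, and power at 66 events is 80.1%. The design therefore treats 10% and 5% as 1 − exp(−10λ), the quantity that one minus Kaplan-Meier estimates.

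**Step 2. Convert to actual cumulative incidence, constant hazards.** Let λ = −ln(1 − KM)/10 and μ = −ln(1 − mortality)/10. Then

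CIF = λ/(λ + μ) × [1 − exp(−10(λ + μ))].

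Example, control arm with 20% mortality: λ = 0.01054 and μ = 0.02231. The bracket is 1 − 0.90 × 0.80 = 0.28, so CIF = 0.3207 × 0.28 = 8.98%.

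| Mortality, both arms | Control (KM 10.0%) | Eradication (KM 5.0%) | Difference (KM 5.00 points) |
|---|---|---|---|
| 5% | 9.75% | 4.88% | 4.88 |
| 10% | 9.50% | 4.75% | 4.75 |
| 15% | 9.24% | 4.62% | 4.62 |
| 20% | 8.98% | 4.49% | 4.49 |

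The overstatement is 0.25 to 1.02 points in the control arm, 0.12 to 0.51 points in the eradication arm, and 0.12 to 0.51 points in the difference. The risk ratio stays at 0.50.

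**Step 3. Unequal mortality.**

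| Mortality, placebo / eradication | Actual difference (KM 5.00 points) |
|---|---|
| 10% / 5% | 4.62 |
| 15% / 10% | 4.50 |
| 20% / 10% | 4.23 |
| 5% / 10% | 5.00 |

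Higher mortality on placebo enlarges the overstatement. In the last row, with higher mortality on eradication, the errors in the two arms cancel in the difference. The cause-specific hazard ratio is 0.487 in every row.

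**Step 4. Late events.** If the event hazard is zero until year 7, then λ = −ln(1 − KM)/3 and

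CIF = exp(−7μ) × λ/(λ + μ) × [1 − exp(−3(λ + μ))].

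For KM 10.0%, this gives 9.6% at 5% mortality (0.9647 × 0.8726 × 0.1137) and 8.3% at 20% (0.8554 × 0.6115 × 0.1583). With 15% mortality on placebo and 10% on eradication, the difference is 4.1 points.

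**Step 5. Hyperplastic polyps.** The article gives no polyp incidence. For an illustrative Kaplan-Meier value of 20.0% with constant hazards, the Step 2 formula gives 19.5% at 5% mortality and 18.0% at 20%.

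**The case against.** The strongest reply is that the planned comparison is sound. With deaths censored, the log-rank test and Cox model compare cause-specific hazards, and under independent censoring unequal mortality does not shift them. This stands. A reader might infer from the Kaplan-Meier choice that the primary test or treatment effect is distorted if mortality differs between arms. The article does not support that: its test is the log-rank test and its effect measure is the hazard ratio. The alpha spending and the 66-event target rest on that test as well.

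Second, the cause-specific comparison better isolates an effect on neoplasms. If eradication had no such effect and mortality were 20% on placebo and 10% on eradication, one minus Kaplan-Meier would show no difference, while actual incidence would differ by 0.52 points. This also stands, and it is a reason to keep the log-rank test and Cox model. It does not make one minus Kaplan-Meier a cumulative incidence.

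Third, the error is small. The trial takes stage 1 patients aged 19 to 70 and excludes severe comorbidity. With 984 × 0.9/2 ≈ 443 patients per arm, the 95% interval for 10% versus 5% is about ±1.96 × √(0.10 × 0.90/443 + 0.05 × 0.95/443) = ±3.5 points, well above the bias. The late-event case is also an extreme: the article's latency is approximate and concerns tumours, while the endpoint includes low-grade adenoma and the design assumes exponential times. This limits the severity.

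Fourth, the article nowhere writes that deaths are censored, and the SAP may add a competing-risk analysis. That is fair: the censoring is an inference, and missing detail is no fault here. But the estimator is named in the article, and a SAP that followed it would carry the problem forward.

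Finally, one cited retrospective study does not show that mortality will differ in this randomized trial. Agreed; the overstatement does not depend on a difference.

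**Conclusion.** The point holds as a minor one. The article fixes an estimator that does not match the quantity it names. Followed as written, it overstates 10-year incidence in each arm, and in most of the cases examined it also overstates the absolute difference. Equal mortality is enough to produce this.

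At an assumed 5% to 20% mortality with constant hazards, the excess is about 0.25 to 1.0 points on 10% and 0.12 to 0.51 points on the 5.0-point difference when mortality is equal. If all events fell in years 7 to 10, the excess on 10% would reach about 1.7 points. Unequal mortality can increase the error in the difference or cancel it. All these sizes rest on assumed mortality, because the article gives none.

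The conclusion does not extend to the log-rank test, the cause-specific hazard ratio or the required number of events.

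**What to change.** In the Statistical analysis section, and in the SAP before it is finalised, state that the cumulative incidence of the composite neoplasm endpoint and of hyperplastic polyps will be estimated by the Aalen-Johansen method, with death before the event as a competing event. Keep the log-rank test and Cox model, described as the cause-specific comparison. Keep Kaplan-Meier for overall survival. Gray's test or a Fine-Gray model may be added as supportive analysis but is optional.

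The cost is a change of wording and a standard SAS option. Deaths are already being collected, and neither the sample size nor the 66-event target changes. The trial is still recruiting and the SAP is to be finalised before code breaking, so the change can still be prespecified. The one downside is that reported incidences will be slightly lower than one minus Kaplan-Meier would show.

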#### Exclusion criteria.

Patients will be excluded if they have the following:

1)history of HPE2)history of previous gastrectomy3)history of any malignancy within the last 10 years4)Patient who previously underwent endoscopic treatment on the section that will become the remnant stomach5)patients who require adjuvant/neoadjuvant chemotherapy6)history of allergy or serious adverse events to prescribed medication, including amoxicillin and clarithromycin7)presence of severe comorbidities (e.g., cardiac, hepatic, or renal insufficiency) or coagulopathy8)pregnant or lactating women9)presence of a psychiatric disorder that might preclude compliance 10)patients who could not provide informed consent 11)Borrmann type 4 tumors (linitis plastica) on tumor classification 12)proximal resection margin shorter than 3 cm in advanced gastric cancer 13)withdrawn consent4Randomization.

Patients will be randomly assigned to one of the two arms in a 1:1 fashion. After the stratification of gastrointestinal reconstruction (distal gastrectomy with Billroth 1 [gastroduodenostomy] or Billroth 2 [gastrojejunostomy] or Roux-en-Y gastrojejunostomy and proximal gastrectomy with double tract reconstruction) methods, centralised stratified block randomization will be used to randomly assign the patients to the two groups.

We have performed a stratified block randomization method using a permuted block design. Stratified randomization is achieved by generating a separate block for each stratification factors, and patients are assigned to the appropriate block of stratification factors. After all patients have been identified and assigned into blocks, simple randomization occurs within each block to assign patients to one of the groups. Because the clinical trial is ongoing, we cannot provide the block size used.

An interactive web-response system will be used for randomization. The patients will be assigned to each treatment group according to the allocation codes provided by the random assignment program, and seeds will be assigned to the random assignment codes to enable reproducibility.

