## Discussion

This double-blinded randomized clinical trial aims to evaluate the effectiveness of HPE in remnant stomach neoplasms after curative gastrectomy. The significance of the current study is described as follows.

First, a pivotal consideration in our research is the deliberate choice of adenoma and adenocarcinoma incidence in the remnant stomach as our primary outcomes. Thus, the effectiveness of HPE in terms of lesions requiring endoscopic or surgical intervention can be directly evaluated as a primary endpoint. Previous RCTs analysed the overall survival or changes in atrophy and metaplasia as primary outcomes; as such, deriving definitive conclusions about the actual impact of HPE on neoplasms in the remnant stomach is challenging [7,9]. With the release of our study results, we will provide critical insights into this matter.

Second, a 10-year long-term follow-up study post randomization will be implemented; thus, the prolonged effects of HPE will be assessed. Tumors that arise in the remnant stomach after curative gastrectomy for gastric cancer treatment require a minimum of approximately 7 years to develop [20–24]. Thus, extended tracking is necessary to investigate remnant stomach neoplasms.

Third, we aim to optimise the randomization process by incorporating the reconstruction method as a stratification factor. This strategic approach is designed to effectively control confounding variables, promote similarity in baseline characteristics, and improve the statistical power of our analysis. Previous research reported variations in the occurrence of remnant gastric cancer associated with different reconstruction methods [19,25–27]. A previous report suggested a higher risk of remnant gastric cancer in patients who underwent proximal gastrectomy, preserving the distal stomach [28]. Therefore, we will include patients who underwent proximal gastrectomy in our protocol. This inclusion is based on our expectation that proximal gastrectomy is associated with a relatively higher likelihood of occurrence of remnant gastric cancer. By incorporating these considerations, our study aims to contribute valuable insights into the reconstruction methods and their implications for remnant gastric cancer risk.

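### Allocation is stratified by reconstruction method, but the log-rank test and Cox model are named without the strata; stating a stratified primary analysis is a small, free improvement

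*Protocol article*

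**What the plan says.** **Allocation.** The randomisation paragraphs, which follow the exclusion criteria in the Protocol article, set a 1:1 ratio and begin the stratification rule with "After the stratification of gastrointestinal reconstruction". The four levels are distal gastrectomy with Billroth 1, Billroth 2 or Roux-en-Y, and proximal gastrectomy with double tract. Within these levels, "centralised stratified block randomization will be used to randomly assign the patients to the two groups".

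**Reason given.** The Discussion describes "incorporating the reconstruction method as a stratification factor" as a way to "promote similarity in baseline characteristics, and improve the statistical power of our analysis". Its support is that "Previous research reported variations in the occurrence of remnant gastric cancer associated with different reconstruction methods", and it expects a relatively higher risk after proximal gastrectomy. It gives no size for these differences.

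**Analysis.** General considerations, under Statistical analysis, plans Kaplan-Meier curves for adenoma, adenocarcinoma, hyperplastic polyps and overall survival, and then: "These will be compared between the two treatment groups using the log-rank test". Hazard ratios come from a Cox model. Neither sentence mentions strata or covariates. The same section leaves full details to an SAP, to be finalised before the code is broken.

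**The concern.** Stratified blocks force the arms to be nearly balanced within each reconstruction method. If reconstruction is prognostic, this balance removes between-stratum variation from the true sampling variance of the log-rank statistic. An unstratified log-rank test still counts that variation in its variance estimate. The estimate is then too large, the statistic varies less than a standard normal, and the test rejects less often than its nominal level. Power falls a little for the same reason.

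Stratified allocation therefore does not by itself deliver the power benefit that the Discussion expects; the analysis has to use the strata as well. The trial aims for only about 80% power from 66 events over ten years, so even a small loss is worth avoiding when it costs nothing. Fixing the choice in advance also avoids having two candidate primary tests that could disagree near the final threshold of 0.049.

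**Working it through.** **1. The plan's own figure.** Inputs from Sample size calculation: 10% ten-year control incidence, a 50% reduction to 5%, two-sided alpha 0.05, about 80% power, 10% dropout, 984 randomised.

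- HR = ln(0.95)/ln(0.90) = 0.4868, stated as 0.49.
- Freedman events = (1.960 + 0.842)² × [(1 + 0.4868)/(1 − 0.4868)]² = 7.85 × 8.39 ≈ 66. This matches the plan.
- Average incidence is (10% + 5%)/2 = 7.5%, so N = 66/0.075 = 880, and 880/0.9 = 978, close to 984. In the other direction, 984 × 0.9 × 0.075 = 66.4 events.

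The formula has no stratification term, so the planned 66 events and 80% power take no credit for stratification.

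**2. Cost of leaving out the strata.** Simulation with 984 patients, exponential event times, 10% dropout, ten years of follow-up, HR 0.49 for power and HR 1 for type I error, one look at |Z| > 1.96, and 25,000 trials per scenario. Both tests were run on the same simulated data. Assumptions not in the article: blocks of 4, stratum shares 30/35/25/10% (proximal gastrectomy last), and the relative hazards below, scaled so that overall control incidence stays at 10%.

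| Relative hazards | Ten-year control risk, proximal | Power, unstratified | Power, stratified | Type I error, unstratified | Type I error, stratified |
|---|---|---|---|---|---|
| 1/1/1/1 | 10.0% | 82.9% | 82.8% | 0.050 | 0.050 |
| 1/1.5/0.8/2 (2.5-fold) | 15.9% | 83.0% | 83.2% | 0.049 | 0.050 |
| 1/2/0.5/4 (8-fold) | 24.6% | 82.4% | 83.3% | 0.046 | 0.050 |
| 1/3/0.3/8 (27-fold) | 32.9% | 81.8% | 83.7% | 0.041 | 0.052 |

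Monte Carlo standard error is about 0.24 points for power and 0.0014 for type I error. Under the null, the standard deviation of the unstratified Z falls from 1.002 to 0.997, 0.979 and 0.955 down the rows, while the stratified Z stays between 0.999 and 1.002. This is the mechanism described above. The power cost is about 0.2, 0.9 and 1.9 points in the last three rows.

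**3. Risk concentrated in one stratum.** The ratio of highest to lowest hazard is not the whole story; it also matters how far events concentrate in one stratum. A second set of runs used 886 patients (984 × 0.9), shares 25/35/30/10% and 6,000 trials per scenario.

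- Relative risks 1/1.5/1/4: power 81.3% unstratified against 82.1% stratified; type I error 4.2% against 4.4%.
- Relative risks 0.5/1/0.5/8: power 78.3% against 83.4%; type I error 3.0% against 5.2%.

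Across four independent runs of 3,000 to 6,000 trials, the power gap was 0.4 to 0.8 points in the first scenario and 5.0 to 5.5 points in the second. In the first scenario, type I error for the unstratified test ranged from 4.0% to 5.0% between runs. That is too noisy to read as a level, so the 25,000-trial table is the better guide.

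**4. What the 5-point case requires.** Let x be the ten-year cumulative hazard at relative risk 1. Solve 0.55(1 − e^(−0.5x)) + 0.35(1 − e^(−x)) + 0.10(1 − e^(−8x)) = 0.10, which gives x ≈ 0.084. The proximal stratum then has a control incidence of 1 − e^(−0.672) ≈ 49%, against 1 − e^(−0.042) ≈ 4% after Billroth 1 or Roux-en-Y.

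The interim look was not simulated. It would affect both tests alike.

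**The case against.** The strongest reply is that the article names families of tests and does not call them unstratified. It defers full details to the SAP, where the choice to stratify by the randomisation factor is commonly made. A stratified SAP analysis would agree with both the randomisation paragraphs and the Discussion. This stands. A reader might infer that the plan has decided to ignore the strata, or that its sections contradict each other, but silence in a condensed article supports neither.

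The reply on size also largely stands. Planned power does not rest on stratification, any error is on the conservative side, and the 5-point loss needs an implausibly sharp contrast that the article does not suggest; it speaks only of a relatively higher likelihood after proximal gastrectomy. A reader might conclude that the trial is underpowered or that the expected power gain is lost. In every scenario except the extreme one, the unstratified test stays above 80%.

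The unstratified hazard ratio is also drawn toward 1 when stratum risks differ, but no size was computed for this, so no weight is placed on it.

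The reply does not remove the case for stating the choice. The article does name the primary test, does link the stratification to power, and does not join the two. In these scenarios stratifying never cost power beyond simulation error.

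**Conclusion.** The point holds as a minor, free improvement. If the primary test is carried out as named, it is valid and slightly conservative. The expected cost is about 1 power point or less under moderate differences between strata, about 2 points at a 27-fold spread, and about 5 points only when nearly half of proximal-gastrectomy controls develop a neoplasm within ten years. Unstratified type I error stays at or below its nominal level apart from simulation error, so a positive result would stand.

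The direction follows from stratified allocation on a prognostic factor. The sizes rest on assumed stratum shares, relative risks and block size, none of which the article gives. The results do not show that the sample size is wrong, and they say nothing about overall survival, hyperplastic polyps or the binary endpoints, for which no figure was produced.

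**What to change.** Add one sentence to General considerations, and carry it into the SAP before code breaking: the log-rank test and the Cox model for the primary endpoint are stratified by the four reconstruction strata used at randomisation, and the unstratified analysis is reported as a sensitivity analysis. The strata are already recorded at randomisation, so this needs no new data, no extra patients and no change to the 66-event target.
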